### Study measurements

#### Quantitative measurements

**Mode and frequency of consultation**

Every presentation of patients in the primary healthcare centre is registered through a coding system that depicts the time of the consultation as well as the condition presenting (e.g., medical treatment during consultation hours, medical emergency). Re-consultations of patients in the primary healthcare centre will also be recorded.
**Reasons for Consultations and Diagnosis**

DCAT encodes automatically the estimated consultation reason as ICPC-2 code based on a patient’s input data [26, 27]. Diagnoses are documented afterwards from the patient notes made by the primary healthcare doctors. These are regularly kept for documentation purposes in the primary healthcare centre in Friedland.
**Age, gender, asylum status, and affiliation to a language group**

Initially, patients using DCAT select their native language or dialect. This selection then directs further audio and visual information. Patient age, nationality, asylum status, sex are also extracted from the patient’s note.
**Acceptance, usability, quality of communication, accuracy of DCAT information, and presence of ad-hoc (lay) interpreters**

When a patient finishes entering his/her data on DCAT, a digital questionnaire follows to assess patients’ experiences with DCAT (see Additional file 1). This questionnaire consists of two parts, the first consists of four questions and is applied directly after using DCAT. These questions seek to evaluate the acceptance and usability of DCAT. The final question regards the educational level of the patients.

The second section of the patient questionnaire follows after the consultation. It has five questions, which focus on the impact of using DCAT in the consultation situation, especially the communication and mutual understanding between the healthcare providers and the patients.

The attending physicians at the Friedland primary healthcare centre are asked to give their feedback on each consultation also using a two-part questionnaire (see Additional file 2). The first section comprises three questions, which ask the doctors their opinions on the perceived quality of communication and mutual understanding throughout the consultation. Whether ad-hoc interpreters are present is also documented. The second set of questions follows only when a medical report (synopsis) is produced through DCAT (see Additional file 3) and asks whether this printed report influences the consultation. Also, any inconsistencies between the DCAT collected information and clinical impressions of the doctors are sought.

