**Methods:**

The study aims to monitor the implementation of a new digital communication assistance tool (DCAT) and to investigate its impact on the mutual understanding between refugee patients and their German general practitioners (GPs). In the first study phase, an action-oriented approach is used to implement DCAT. In the second study phase, DCAT use will be evaluated with a mixed methods design.

The main outcome assesses the re-consultation rates of patients before and after using DCAT. Secondary outcomes include the usability of the tool, its acceptance and perceived quality by patients, the accuracy of the information collected as determined from analysing the reasons for the consultation (ICPC-2 codes), and diagnosis (ICD-10 codes). The acceptance by patients, socio-demographic factors and native language are also taken into account.

The research designs for both study phases include questionnaires, semi-structured interviews, non-participant observation and analysis of collected patients’ data.

All the collected data is pseudonymised.

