As a secondary outcome, the following are to be assessed:The perceived quality of the communication in the consultation by both patients and healthcare professionals. After each consultation patients are asked to fill in questionnaires about their perceptions around mutual understanding with the attending physician.The perception of the usability and acceptance of the tool by patients and GPs, which is also gauged through questionnaires after each consultation.The usability and acceptance of DCAT by different patient subgroups according to age, gender, country of origin, asylum status, educational level and spoken languages. When patients decide to stop using DCAT, this will also be registered.The accuracy of collected information through DCAT. The aim is to clarify whether DCAT can be reliably utilised and incorporated into the clinical decision-making process to improve healthcare outcomes [20, 21]. DCAT estimates the reasons for the encounter as ICPC-2 codes based on the information provided by the patient, and doctors will also be indicating their diagnosis (ICD-10 codes). We want to compare the DCATs estimated reasons for a consultation and the GP’s diagnosis in terms of plausibility and contingency to investigate the accuracy of the provided medical information by DCAT [22]. Also, GPs will be asked after each consultation through questionnaires if their impression of the patient’s description contradicts the information provided by DCAT.

For a deeper insight into the acceptance of DCAT users, we will apply qualitative research methods, namely:Use of open and partially standardised interviews conducted with healthcare workers (GPs and nurses) and a group of selected patients in the refugee camp.The researchers also will explore the use of DCAT as a non-participant observer.

The research design of the DCAT Study is shown in Fig. 1.

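### By the procedure described, education has no source for patients who stop DCAT early, and patient-rated mutual understanding has no control measurement

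*Protocol article*

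**What the plan says.** The Protocol article describes one patient questionnaire, in Study measurements under the heading that begins with acceptance and usability. Its trigger is: "When a patient finishes entering his/her data on DCAT, a digital questionnaire follows". Its purpose is to capture how patients experienced the tool.

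- **Part one:** "the first consists of four questions and is applied directly after using DCAT". Of its content the article says "These questions seek to evaluate the acceptance and usability of DCAT", and then "The final question regards the educational level of the patients".
- **Part two** comes after the consultation: "It has five questions, which focus on the impact of using DCAT in the consultation situation", with emphasis on communication and mutual understanding.

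The physician questionnaire in the same section is built differently. Its first part is asked at each consultation, and only its second part depends on a DCAT report having been produced.

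The Design section lists the secondary outcomes that use these data:

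- communication quality as perceived by patients and professionals;
- usability and acceptance;
- both of the latter by age, gender, country of origin, asylum status, education and language.

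Within the subgroup item it adds: "When patients decide to stop using DCAT, this will also be registered". The same list says that patients complete questionnaires on mutual understanding following every consultation, without restricting this to DCAT users.

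**The concern.** Two things do not connect.

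First, education is placed at the end of a block that follows completed data entry. A patient who gives up midway is recorded as having stopped, but no step is described that would capture that patient's education or ratings. The article itself expects difficulty with reading and writing (Recruitment and informed consent) and unfamiliarity with the technology (Discussion). Education is thus a variable against which one would want to see stopping.

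Second, the Abstract states an aim about DCAT's effect on mutual understanding, and the Design section presents a comparison of users with non-users. The only patient items described for mutual understanding ask about the effect of using DCAT, which a non-user cannot meaningfully answer. If the plan is followed as described, the patient ratings have no comparator. A high score could then reflect the tool, or simply how these patients rate any consultation.

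**Working it through.** The plan states no figure on this point, so the main check sets its sections side by side.

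**Step 1: source of each breakdown variable (Design section against Study measurements)**

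| Variable | Described source | Depends on finishing DCAT? |
|---|---|---|
| Age | patient's note | no |
| Gender | patient's note | no |
| Country of origin | patient's note (as nationality) | no |
| Asylum status | patient's note | no |
| Language | selected when DCAT starts | no |
| Education | last question of part one | yes, as described |

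Five of the six variables exist for anyone who launches DCAT. Education is the exception. Stopping can be tabulated by the other five but not by education.

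**Step 2: who supplies ratings of mutual understanding**

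| Rater | DCAT users | Non-users |
|---|---|---|
| Physician, part one | each consultation | each consultation |
| Patient, part two | after the consultation, about DCAT's impact | no version described |

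With the planned group sizes, patient ratings come from at most 440 DCAT patients and, by the procedure described, from 0 of 440 controls.

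**Step 3: planned comparison.** The Data analysis section announces tests between study and control groups without naming outcomes. Its one named test of perceived communication sets DCAT patients against their own physicians. That measures agreement between two raters of the same consultation. It does not measure the effect of the tool.

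**Step 4: illustration of size.** Let s be the share who stop, a_f acceptance in finishers and a_s acceptance in stoppers.

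Acceptance among all who launch = (1 − s)·a_f + s·a_s

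Overstatement if only finishers are rated = a_f − [(1 − s)·a_f + s·a_s] = s·(a_f − a_s)

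All values of s, a_f and a_s below are assumptions, since the article gives none.

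| s | a_f = 80%, a_s = 40% | Overstatement | a_f = 85%, a_s = 0% (extreme) | Overstatement |
|---|---|---|---|---|
| 10% | 0.90×80 + 0.10×40 = 76% | 4 points | 0.90×85 = 76.5% | 8.5 points |
| 20% | 0.80×80 + 0.20×40 = 72% | 8 points | 0.80×85 = 68.0% | 17 points |
| 30% | 0.70×80 + 0.30×40 = 68% | 12 points | 0.70×85 = 59.5% | 25.5 points |

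At 10, 20 and 30% stopping, 44, 88 and 132 of 440 users would lack part one. The direction of the bias holds whenever stoppers accept the tool less than finishers do.

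**The case against.** The strongest reply is that the Design section has patients rating mutual understanding after every consultation, in wording that could include controls, and that the questionnaire itself (Additional file 1) is not shown. This stands to the extent that a reader might infer that control ratings are certainly absent, and the documents do not establish that. It does not remove the problem. If controls are included, the Design section conflicts with a questionnaire that follows DCAT entry and asks about DCAT. If they are not, there is no comparator.

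A reader might also infer that acceptance is wholly missing for stoppers, or will be calculated among completers. Neither is supported. Stopping is registered within the acceptance outcome, no denominator is stated, and the article does not say what happens to the questionnaire after an early exit. What lacks a described source is the stoppers' education and ratings.

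Nor does the article show that the patient side of the aim is unanswerable or that bias is greatest in older or less literate patients. Interviews and observation also capture patients' views, physician ratings cover each consultation, and audio and visual content is built in for those who read poorly.

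Finally, scoring every stopper as non-accepting can err in the other direction, because a patient may stop for reasons unrelated to the tool. That objection is sound and is reflected in the fix.

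**Conclusion.** The point holds in a limited form. As described, education cannot be linked to early stopping, and the questionnaire ratings of acceptance and usability describe finishers. Patient-rated mutual understanding has no described control measurement, and the Design, Study measurements and Data analysis sections need to be reconciled on who receives the patient questionnaire.

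The size of any overstatement of acceptance is unknown. The 4 to 12 points in the milder illustration and the 8.5 to 25.5 points in the extreme one rest wholly on assumed stopping and acceptance rates, and on ratings being summarised among finishers.

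Only secondary outcomes are touched. The primary outcome comes from the centre's registration of consultations and is unaffected. The matter is worth correcting because the remedy is cheap.

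**What to change.** Before the DCAT version is fixed at the end of the first phase:

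1. Move the education question to launch, next to language selection.
2. Offer the acceptance items on early exit as well as on completion.

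In the outcome definitions and analysis:

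3. Report completion and stopping over all who launch DCAT, by each subgroup, beside the ratings among those who respond. Count stoppers as non-accepting only in a sensitivity analysis.
4. Name part one of the GP questionnaire as the user-versus-non-user communication outcome. It is already asked at each consultation.
5. State who receives the patient questionnaire, in the same terms in the Design, Study measurements and Data analysis sections. Label patient ratings as uncontrolled and descriptive, unless items that do not mention DCAT are also given to non-users.

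The cost is a reordering of screens and some rewording, with no extra patients or visits. Giving neutral items to non-users would add a short questionnaire in that group. The downside is small: one question comes before the history, and the acceptance figure may be less favourable.

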#### Qualitative measurements

Throughout each phase of the DCAT study, the experiences of both healthcare professionals and patients with the intervention will be collected to understand DCAT effects and any additional questions. The research team will perform open and partially standardised interviews with healthcare workers (primary healthcare doctors and nurses) and a group of selected patients in Friedland [28].

The researchers also will periodically act as non-participant observers when patients are using the tool. This type of observation has proved its merit in earlier studies regarding objectivity and careful analysis [29, 30]. Additional comments will be collected and discussed with social workers and healthcare personnel to assess any issues and to react accordingly. Data will be collected in the form of field notes.

### Data management

Every patient in the DCAT study will receive a unique digital readable label (QR-Code), which is placed on his/her identification card (ID) in order to pseudonymise patient’s data. The social service workers issue these IDs to all refugees and asylum seekers after their arrival to Friedland. DCAT is launched after scanning the QR-Code. Therefore, the printed report, which has the QR-Code, can only be reassigned back to the patient by medical staff at the primary healthcare centre. Thus in case a report is lost, no one can identify it, which safeguards the patient’s personal as well as medical data.

Personal information allowing patient identification (e.g. first and last name) is not collected by DCAT. The collected data is not shared with other authorities or third parties. All other information not described above, e.g. health-related information given by the patient through DCAT is deleted permanently. The pseudonymised patient notes are evaluated by the research team and coded according to diagnosis (ICD-10 codes) [22].

All quantitative and qualitative data is only accessible by the study team. The study team is familiar with data privacy regulations and committed to data protection principles. A data monitoring committee is not needed in this trial because of the relatively short study period and the minimal risks to patient safety using the DCAT in comparison to randomised controlled trials on drugs and biologics.

All collected data will be permanently deleted ten years after the study.

### Data analysis

The quantitative data will be analysed using SPSS (version 25.0) on the basis of descriptives (i.e., frequencies and means). Differences between patients of the study group and the control group will be tested for statistical significance. Furthermore, differences between patients using DCAT and their physicians regarding their opinions on the perceived quality of communication and mutual understanding throughout the consultation will be tested for significance.

The qualitative data (interviews with GPs, nurses and patients) will be audio-recorded. Two members of the team will code the interview transcriptions and analyse them by the summarising qualitative content analysis [31].

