### Recruitment and informed consent

Participating in the study and utilising DCAT is voluntary. Written informed consent is collected from each patient (or from the parents for patients under 18 years) willing to participate before using DCAT. All participants have the right to withdraw from the study at any point and all their collected information is immediately deleted.

Since the DCAT study is restricted to non-German-speaking patients, who might also have difficulties in reading and writing, audio- and visual content in the chosen language has been incorporated into DCAT [15, 16].

The potential participants are informed of the DCAT study directly on their arrival in Friedland camp through interpreters and social service workers. There are also posters and flyers (available in different languages) describing DCAT distributed across various sites in Friedland. Due to the structure of the referral system in Friedland, which mandates that asylum seekers need to get a permit from the responsible social service worker before being referred to the primary healthcare centre, we also included the social service bureau as a recruiting location in this study (see Fig. 4).

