### Sample size calculation

The sample size calculation is based on the average numbers of patients in the last 12 months in Friedland. Due to fluctuations in refugee flows (ranging from 285 to 636/month), it is difficult to predict how many patients will be treated at the primary healthcare centre during the study period and meet the inclusion criteria, especially regarding the available languages. Despite these uncertainties, during the six months recruitment period we aim to include a total sample size of 880 participants (study group: 440 patients using DCAT, 440 patients not using DCAT). The sample size calculation is based on the consultation rates for medical treatment at the primary healthcare centre in Friedland as this is the primary outcome of the study protocol. Our previous research in the preparation phase revealed an average consultation rate for medical treatment of 2.65 (SD: 3.44) consultations per patient. Assuming a 10% dropout rate, to measure a minimal difference of 0.65 consultations per patient, 5% significance (two-sided) and a standard deviation of 3.5, 20 patients should be recruited per week to use DCAT to achieve the identified sample target.

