It should be noted however that DCAT is neither able to make a diagnosis nor can it give medical advice. It is an aid for doctors to obtain the medical history (symptoms and signs) from the patient perspective without the need for interpreters and translators.

We do expect some possible challenges with our study design. As this digital communication assistance tool is newly developed and its adoption will likely change the daily routine at the medical consultation, we are expecting some reluctance to use it, especially on the part of the healthcare provider. Such potential difficulties may require additional DCAT revisions during the study to ensure the quantitative as well as qualitative research goals (extension of the initial 18 month study period, changing the locations, where the patient can use DCAT, changing routine, e.g. admission times).

We also anticipate that not all patients will utilise DCAT because of unfamiliarity with the technology involved or the unavailability of some spoken languages at the primary healthcare centre in Friedland. During the study period, we will find out about such possible limitations and obstacles that might prevent DCAT usability.

In conclusion, this study remains an essential step to assess the potential effectiveness of the DCAT tool in facilitating communication and removing language barriers to improve the quality of the healthcare encounter for patients who do not speak German.

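### The primary comparison of DCAT users with non-users is self-selected, but the analysis section names no control of confounding

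*Protocol article*

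**What the plan says.** The Design section of the protocol article sets the primary outcome as the consultation rate of DCAT users against that of non-users. On how the groups arise, Recruitment and informed consent states: "Participating in the study and utilising DCAT is voluntary". The Discussion anticipates that "not all patients will utilise DCAT because of unfamiliarity with the technology involved or the unavailability of some spoken languages" at the centre. No randomisation or other allocation is described.

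For the comparison itself, Data analysis names descriptives (frequencies and means) and then says: "Differences between patients of the study group and the control group will be tested for statistical significance". The Sample size calculation plans "study group: 440 patients using DCAT, 440 patients not using DCAT" to detect "a minimal difference of 0.65 consultations per patient, 5% significance (two-sided) and a standard deviation of 3.5".

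Several covariates are available. The measurements section says: "Patient age, nationality, asylum status, sex are also extracted from the" patient's note. In the Design section such variables serve to describe usability and acceptance by subgroup. The Abstract says that socio-demographic factors and native language are considered, without saying how or for which outcome.

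A supported language is an inclusion criterion (Participants and inclusion criteria). The only capture of language that is described is the patient's own selection on starting DCAT.

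**The concern.** When patients choose their own group, the groups differ for reasons other than the tool, and a significance test cannot separate these from its effect. The protocol itself supplies a plausible route. The camp houses resettlement refugees and asylum seekers (Study setting). Asylum seekers need a social worker's permit before referral to the healthcare centre, and the social service bureau was added as a recruiting location for that reason (Recruitment and informed consent). Asylum status may therefore affect both the chance of using DCAT and the number of consultations. Length of stay in a transit camp could act in the same way, since a longer stay gives more opportunity for both.

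The aim section expects the results to indicate the effectiveness of DCAT. If the analysis stops at what is written, a significant result could not be attributed to the tool, and a null result could hide a benefit.

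**Working it through.** **Inputs from the Sample size calculation:** mean and SD from earlier work, "2.65 (SD: 3.44) consultations per patient"; difference 0.65; planning SD 3.5; two-sided 5%; 440 per group; "Assuming a 10% dropout rate". Power is not stated; 80% is assumed here.

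**1. The plan's own figure.** For an unadjusted comparison of two means, n per group = 2 × (1.960 + 0.842)² × SD² / 0.65².
- SD 3.5: 455.1, so 456; divided by 0.9 for dropout, 507.
- SD 3.44: 439.7, so 440, with no allowance for dropout.

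The stated 440 is therefore matched by a plain two-mean comparison using the observed SD, but not by the stated SD of 3.5 with 10% dropout. At 20 users per week, 26 weeks would give 520, or 468 after dropout, so 440 may be meant as the evaluable number. Both 440 and 396 (440 × 0.9) are carried forward.

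**2. Standard error of the unadjusted difference.** SE = 3.5 × √(2/n).
- n = 440: 0.236.
- n = 396: 0.249.

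**3. Bias from one binary factor.** Bias = (difference in its prevalence between groups) × (difference in mean consultations between its levels). Both terms are assumptions; the documents give neither.

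**4. Rejection rate under a true null.** Rate = 1 − Φ(1.96 − bias/SE) + Φ(−1.96 − bias/SE).

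| Assumed imbalance | Assumed shift (visits) | Bias | Rate, n = 440 | Rate, n = 396 |
|---|---|---|---|---|
| 10 points | 1.0 | 0.10 | 7.1% | 6.9% |
| 20 points | 1.0 | 0.20 | 13.5% | 12.7% |
| 30 points | 1.0 | 0.30 | 24.6% | 22.6% |
| 20 points | 2.0 | 0.40 | 39.6% | 36.3% |

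A bias of 0.40 is 0.40/0.65 = 62% of the target difference.

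**5. What adjustment does to power.** Effective SD = 3.5 × √((1 − R²) × VIF), where R² is the share of variance the covariates explain and VIF is the variance inflation from imbalance between groups. Both are assumed. Power to detect 0.65 with 396 per group:
- R² 0, VIF 1.0: 74.3% (no gain, no loss).
- R² 0, VIF 1.25: 64.7%.
- R² 0.10, VIF 1.1: 74.7%.
- R² 0.20, VIF 1.0: 83.2%.

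If the imbalance were strong enough for a VIF of 1.5 with R² 0, power would fall to 56.9%.

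**The case against.** The best defence is that the article does not say the comparison will be unadjusted. It is a condensed account, the SAP is not shown, and model form and covariates are often left to a SAP. The Abstract says these factors are considered. A reader might infer that the sponsor has committed to a raw comparison; the text does not go that far. That stands as a limit on the wording. It does not dispose of the point, because in a non-randomised study the control of confounding is part of the design, and the analysis section that is given contains nothing that provides it.

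A reader might also infer that speakers of unsupported languages will sit among the 440 controls. The documents do not support this. A supported language is an inclusion criterion for all participants, and the Sample size calculation refers to it just before setting the target. The Discussion says only that some patients will not use the tool. What remains is that it is unclear how a control's language is established.

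The 40% figure needs a 2-visit gap, about 75% of the mean of 2.65 (2/2.65), together with a 20-point imbalance. It shows what could happen and is not a forecast for this study.

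Finally, the Abstract describes the main outcome as before versus after DCAT use, while the Design section compares users with non-users. That has to be settled first; the point here applies to the Design section's comparison, which the sample size also uses.

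**Conclusion.** The concern stands in this form: the primary user versus non-user contrast is self-selected, and the plan as written names no means of controlling confounding, although four relevant covariates are already collected. The direction and size of the bias are unknown. Under assumed biases of 0.2 to 0.4 visits the nominal 5% error becomes about 13% to 40%; under a bias of 0.1 it is about 7%.

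It would be too much to infer that adjusting for these covariates makes the comparison causal. Familiarity with technology, one of the authors' own reasons for non-use, is not among the recorded variables described. Education is asked in the questionnaire that follows DCAT entry, so it may be missing for non-users. The framing is partly exploratory, but the stated aim of indicating effectiveness is enough to make the omission matter.

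**What to change.** - **Primary analysis.** State a regression of consultations per patient on DCAT use, adjusted for age, sex, nationality and asylum status, and accounting for length of stay where available. Report the adjusted mean difference with a 95% confidence interval, which keeps the result on the scale of the 0.65 target. Give the unadjusted difference as supportive. If a count model with a rate ratio is preferred, it needs a term for time at risk and a conversion back to a mean difference.
- **Interpretation.** Call the result an adjusted association, and name technology familiarity and education as uncontrolled or possibly missing for non-users.
- **Controls.** State explicitly that the language criterion applies to non-users and record their language, for example when the ID card is issued. Reconcile Participants and inclusion criteria with the remark on unavailable languages in the Discussion.
- **Primary comparison.** Settle the Abstract's before/after wording against the Design section.

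**Cost:** a few lines of analysis text and one language field for controls; the four covariates are already extracted. Length of stay may need to be obtained. Adjustment is not free in precision: power is about 65% to 83% at 396 per group for R² of 0 to 0.20 and VIF of 1.0 to 1.25, so the sample size should be rechecked. Residual confounding remains.

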### Study population

#### Participants and inclusion criteria

In this study, informed participants can use DCAT:At the primary healthcare centre for patients seeking medical care andAt the social service bureau referral point.

All patients who meet the following inclusion criteria are eligible to participate in the study:Patients who speak one of the following languages: Arabic, Kurdish, Turkish, Persian, Pashto or any of the following dialects: Modern Standard Arabic (MSA), Arabic Syrian, Arabic Egyptian, Arabic Tunisian, Arabic Moroccan, Kurdish Sorani, Kurdish Kurmanji, Kurdish Feyli, Pashto Kandahari, Pashto Mazurka.The patients (or in case of children their parents) provide written informed consent before participating in the DCAT study.

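### Relatives can enrol as separate patients, but the sample size carries no design effect and the listed data include no family identifier, so within-family correlation may be impossible to handle at analysis.

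*Protocol article*

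**What the plan says.** - **Eligibility** (Participants and inclusion criteria). Any patient who speaks a listed language and has consented may take part: "The patients (or in case of children their parents) provide written informed consent before participating in the DCAT study". Recruitment and informed consent repeats that parents sign for patients under 18. Neither section limits the number of patients per family.
- **Sample size** (Sample size calculation). The target is "study group: 440 patients using DCAT, 440 patients not using DCAT". The inputs are "an average consultation rate for medical treatment of 2.65 (SD: 3.44) consultations per patient" from earlier work, "Assuming a 10% dropout rate, to measure a minimal difference of 0.65 consultations per patient" and "5% significance (two-sided) and a standard deviation of 3.5". Power is not stated, and no allowance for clustering appears.
- **Analysis** (Data analysis). "Differences between patients of the study group and the control group will be tested for statistical significance". No test, model or standard-error method is named.
- **Data recorded** (Study measurements; Data management). The listed items are consultations, reasons for encounter, diagnoses, age, sex, nationality, asylum status, language, education and questionnaire answers. Each patient gets an individual QR label on the identification card: "The social service workers issue these IDs to all refugees and asylum seekers after their arrival to Friedland". No family or household code is listed, DCAT does not collect names, and Data management says that information it does not describe is permanently deleted.

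**The concern.** A parent who enrols may also enrol one or more children, and each counts as a patient towards the 880. Consultation counts of relatives may resemble each other, because they share infections, habits of seeking care and length of stay. Relatives may also tend to share DCAT status. They usually share a language, and the Discussion names missing languages and unfamiliarity with the technology as expected reasons for non-use. A young child also depends on a parent to consent and to handle the device.

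If both outcome and group are shared within families, 440 patients carry less information than 440 unrelated patients. The interval for the 0.65 difference would then be too narrow, and a true null would be rejected more often than 5% of the time. The practical risk is that no analysis can correct for this unless the data show who is related to whom.

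**Working it through.** **1. Reproducing the planned figure.** Inputs from Sample size calculation: difference 0.65, two-sided 5%. Power is assumed to be 80%, because none is stated. The formula for independent patients is n per group = 2(1.96 + 0.84)² × SD² / 0.65².

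- With the observed SD of 3.44: n = 439.7, so 440. This matches the stated group size with no design effect and no dropout.
- With the planning SD of 3.5: n = 455.1, so 456, and 456/0.9 gives 507 after 10% dropout. This does not match 440. That mismatch is a separate matter. Here it matters only that the one combination that yields 440 at 80% power leaves no room for clustering.

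**2. Power as planned.** At 440 per group and SD 3.5 the standard error is 3.5 × √(2/440) = 0.236. Then 0.65/0.236 = 2.75, and power = Φ(2.75 − 1.96) = 79%.

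**3. Are co-enrolled relatives plausible?** The same section gives a flow of 285 to 636 per month. Over six months that is 1,710 to 3,816 people, so 880 would be 880/3,816 = 23% to 880/1,710 = 51% of them. At such a sampling fraction some relatives are likely to be enrolled together. The article does not say how many.

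**4. Relatives in the same group.** The mean number m of enrolled members per family and the within-family correlation (ICC) are assumptions. Design effect DE = 1 + (m − 1) × ICC. The true type I error of a patient-level 5% test is 2 × [1 − Φ(1.96/√DE)]. Power of a valid test is Φ(2.75/√DE − 1.96), using the unrounded 2.7546.

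| m | ICC | DE | True SE / patient-level SE | Type I error | Power at 440 per group |
|---|---|---|---|---|---|
| 1.5 | 0.05 | 1.025 | 1.01 | 5.3% | 78% |
| 2 | 0.10 | 1.10 | 1.05 | 6.2% | 75% |
| 2 | 0.30 | 1.30 | 1.14 | 8.6% | 68% |
| 3 | 0.30 | 1.60 | 1.26 | 12.1% | 59% |

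The formula takes families of equal size. With unequal sizes at the same mean, the design effect is somewhat larger.

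**5. Families split evenly between groups.** Here DE = 1 − ICC, and the error reverses.

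- ICC 0.10: the true SE is √0.90 = 0.95 of the patient-level SE, and type I error is 3.9%.
- ICC 0.30: the ratio is √0.70 = 0.84, and type I error is 1.9%.

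**The case against.** A reader might infer that the primary standard error is too small, or that the plan tests 880 patients as independent. The article supports neither as a statement of fact.

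- **No test is named.** The choice of standard error commonly sits in a full protocol or analysis plan, which is not shown. Its absence from an article is not an error. This stands, so the point rests on the sample size and the recorded data, not on the wording of Data analysis.
- **The direction is not fixed.** The article gives no family size, no correlation, no share of patients with an enrolled relative and no rule that places relatives in one group. Use of DCAT is voluntary, and unfamiliarity with technology can differ between relatives. Parental consent to take part is not the same as a parental decision on use. This also stands: shared status is plausible but not stated, and split families would make a patient-level test conservative.
- **The comparison itself is described in two ways.** The Abstract speaks of rates before and after DCAT use, the Design section of users against non-users. The calculation above applies to the second. If before and after means within the same patient, family-level exposure does not arise in this form.
- **Self-selection into use is a separate threat** that a robust standard error does not touch. This stands as a limit on what the fix achieves.

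What the objection does not remove is the data gap. An unseen analysis plan can choose a clustered standard error, but it can apply one only if relatives can be identified, and the listed data suggest that they cannot.

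**Conclusion.** The point holds in conditional form. Relatives can be counted as separate patients, 440 per group fits the independent-patient formula at an assumed 80% power, and no family identifier is listed. Whether a patient-level standard error would be too small or too large depends on facts that the article does not give.

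Under the assumed range, with all relatives in one group, the design effect is 1.03 to 1.60, type I error is 5.3% to about 12%, and power falls from 79% to between 78% and 59%. At the low end the effect is negligible. The upper figures need three enrolled members per family on average and a correlation of 0.3. This is a modest and inexpensive improvement. It does not show that the primary result will be wrong.

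**What to change.** 1. **Data management:** record a pseudonymous family code when the QR label is attached to the identification card, and list it among the retained data.
2. **Data analysis:** use family-clustered (robust) standard errors for the primary comparison. These are valid whether relatives share a group or split, so no assumption about direction is needed. With 880 patients and 1.5 to 3 members per family there would be about 880/3 = 293 to 880/1.5 = 587 families, enough for the method.
3. **Sample size calculation:** keep the target and report the power of 440 per group over an assumed range of design effects, such as the table above.

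The cost is one extra code per patient, a small added privacy burden because relatives become linkable, and usually a slightly wider interval. No further patients are enrolled, so any loss of power is disclosed and not recovered. Bias from self-selection into DCAT use remains and needs its own treatment.
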